#### IV. Control group/Minimal Intervention

For ethical reasons (nonmaleficence/preventing harm; fairness/equitable access), the control group cannot be completely excluded from any intervention [55]. Therefore, a minimal intervention comprising six educational posters, which are the same as those utilized in the awareness training intervention (*see above*), are displayed in the classrooms. The posters display six key points, the same as in the awareness arm booklet, and provide contact details for the local healthcare services and healthy lifestyle groups. Pupils who recognize their own need for help have the opportunity to contact (self-referral) healthcare providers or a healthy lifestyle group. This minimal intervention for the control group includes no other form of intercession.

The posters hang in the classroom for four weeks, as all interventions performed in SEYLE have an active intervention period of 4 weeks.

### Pupil referrals in each intervention

During and after the SEYLE interventions, students at-risk are actively referred to local health-care facilities and to healthy lifestyle groups. Students are referred according to the arm they were randomized to. In the QPR arm, teachers and school staff refer pupils; in the Awareness and Control arms, pupils self-refer; and in the Professional Screening arm, the healthcare professional refers the pupils. Pupil consignment is based on the level of risk for each pupil.

### 3- and 12-month follow-up assessment for pupils

The assessment instruments used for the baseline measurement (GSHS, WHO-5, PSS, SDQ, BDI, DSHI, EVS questions and SEYLE-specific questions) are also used for the 3- and 12-month follow-up evaluations. These measures cover the same outcome variables as those in the baseline assessment in order to investigate changes. The follow-up questionnaire also includes key questions covering information on the use of referrals by teachers, school staff, health professionals and self-referrals. The follow-up assessment comprises the description of treatment received, as well as an evaluation of the intervention study activities performed by teachers, school staff and health professionals.

### Outcome measures

Outcome variables that are assessed in the project include well-being, depression, anxiety, emotional and conduct problems, coping, self-destructive and addictive behaviors, values, and lifestyles. Table 3 illustrates the outcome variables and the corresponding assessment tools utilized to measure them.

**Table 3 T3:** Correspondence between questionnaire measures and study outcomes

Tool for measurement	Outcome variables
WHO-5	General well-being

Beck Depression Inventory (BDI)	Depression

Paykel Suicide Scale (PSS)	Suicidal behavior

Global School-Based Pupil Health Survey (GSHS)	Alcohol use and abuse
	
	Drug use and abuse
	
	Eating habits
	
	BMI
	
	Physical activity
	
	Sexual habits
	
	Tobacco use
	
	Violent behaviors
	
	Risky behaviors

Strengths and Difficulties Questionnaire (SDQ)	Emotional symptoms
	
	Conduct problems
	
	Hyperactivity/inattention
	
	Peer relationship problems
	
	Pro-social behavior

European Values Study Questionnaire (EVS)	Values (religion, family, marriage, work, friendship)

Specific SEYLE questions	Coping
	
	General child health
	
	Peer relations
	
	Child-parent relations
	
	Stigma and discrimination
	
	Future outlook

Deliberate Self Harm Inventory (DSHI)	Self-harm behavior

Young's Diagnostic Questionnaire (YDQ) for Internet Addiction	Internet addictive behavior

Another outcome variable is pupil referrals, i.e. the total number of referrals inclusive all emergency cases identified during the baseline evaluation, and treatment outcomes. For data collection, SEYLE has developed a systematic method of recording and monitoring all referrals and obtaining feedback on their appropriateness. Pupils are asked whether they have been referred and to whom, what kinds of treatment they have received (medication, psychotherapy, both or neither etc.) and for how long. Phone calls are performed with pupils who do not participate in the follow-up evaluations, and, where possible, facilitators maintain contact with the pupils' parents. In cases, where parents or family represent a source of concern in the perception of the pupil or staff member, contacts will be handled in a particularly careful manner [56].

### Professionals, teachers and school staff assessment

Baseline and 3- and 12-month evaluations is also performed among health professionals, teachers and school staff involved in the project. Health professionals are assessed by a short 12-item questionnaire on their knowledge and preparedness of treating adolescents displaying suicidal behaviors. Teachers and school staff undergo a more detailed assessment questionnaire that collects data on mental health and suicidal behavioral knowledge, perception and attitudes towards mental health and suicide, employment satisfaction, their personal well-being and perspective of the SEYLE project.

### Data analysis

The SEYLE project generates a total sample of 11,000 European adolescents, with 8,250 (750 per site) receiving one or other of the three interventions being tested. The control arm contributes 2,750 adolescents (250 per site) to the total sample.

Power calculations adhere to the widely accepted proposals made by Cohen (1988) [57] for detection of small, medium and large effects. For all outcome measures, the sample size gives the study more than 80% statistical power to detect medium effects within the individual centers and small effects at the aggregate level of centers. Overall, the SEYLE intervention project is expected to show medium effect changes.

The SEYLE study sample potentially exceeds the sample size requirements in order to detect statistically significant changes. This will ensure the required statistical power, taking into account the possibility of some center recruiting fewer pupils than expected, attrition rates at follow-up and missing data. An initial stage of statistical analysis involves examining the consistency of psychometric properties across sites of the measures used in the SEYLE study. Reliability analysis is performed on the relevant data from each participating center. The suitability of continuous variables for parametric tests is assessed.

In cases where the diagnostics indicate that the reliability of the parametric tests may be significantly undermined, the appropriate non-parametric test is carried out. These include the Mann-Whitney test, the Kruskal-Wallis test, the Wilcoxon test and Friedman's ANOVA. Comparisons between study arms in relation to dichotomous and polychotomous variables are initially made using Fisher's exact test and chi-square tests, as appropriate. Logistic regression compares the intervention arms to the control arm in relation to the risk of an event of interest occurring in the follow-up period. The odds ratio, with its 95% confidence interval, is used as the measure of relative risk. An adjusted odds ratio is produced from multivariate logistic regression models, which include relevant covariates. Statistical analyses are carried out at the level of the individual centers and at the aggregate level. Variation in the experimental effects is examined across the 11 participating centers.

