### Population and sampling procedures

The target sample for each intervention 'arm' as well as for the control 'arm' is 250 pupils, i.e. 1,000 subjects in each participating country (totaling 11,000 subjects overall).

In each study site, a catchment area is identified and a list of eligible schools generated. Eligible schools are categorized by size as (1) **small **(less than or equal to the median number of pupils in all schools in the study catchment area or region) and (2) **large **(greater than the median number of pupils in all schools in the study catchment area or region). Every class in each school selected (regardless of size) where 15-year-old pupils make up a majority is surveyed. This age group is selected because of its risk propensity and the feasibility of performing 12-month follow-ups. Schools are randomized on the basis of their size category and sequentially assigned to respective intervention and control arms, comprising both large and small schools. The remaining large and small schools are then sequentially numbered.

To avoid contamination and confounding, only one type of intervention is performed in each school. Given the insufficient evidence of effectiveness of the interventions, equipoise can be assumed so that no institution or group will be put at (dis)advantage systematically. Schools are only aware of the respective intervention arm implemented at their facility, i.e. pupils are not informed of the other types of intervention performed in other schools. The effect that information could eventually spread through informal suggestions can be neglected; in case this becomes a topic, project members would apply a strategy to openly give appropriate additional information. A coordinator is assigned to each intervention arm and its implementation. Coordinators in the respective schools for each arm are instructed only on how to implement their own intervention arm, and have no prior experience of the procedures for the other interventions. Informed consent to participate in the study is obtained from all the adolescents and their parents.

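### The blanket claim of over 80% power for every outcome holds for continuous scales but not for low-frequency binary outcomes such as suicide attempt, above all within single centres

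*Protocol article*

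**What the plan says.** The Data analysis section explains the basis of the sample size: "Power calculations adhere to the widely accepted proposals made by Cohen (1988) [57] for detection of small, medium and large effects". It then makes one power statement for every outcome: "For all outcome measures, the sample size gives the study more than 80% statistical power to detect medium effects". The two levels are "medium effects within the individual centers and small effects at the aggregate level of centers". It adds: "Overall, the SEYLE intervention project is expected to show medium effect changes".

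The numbers behind the statement are 250 pupils per arm in each country (Population and sampling procedures: "The target sample for each intervention 'arm' as well as for the control 'arm' is 250 pupils") and 2,750 per arm over 11 countries (Data analysis: "The control arm contributes 2,750 adolescents (250 per site) to the total sample").

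Table 3 under Outcome measures lists suicidal behaviour, measured by the Paykel Suicide Scale, and self-harm among the outcomes. The Data analysis section plans logistic regression of each intervention arm against control "in relation to the risk of an event of interest occurring in the follow-up period". On the effect measure it says: "The odds ratio, with its 95% confidence interval, is used as the measure of relative risk". These analyses are to be run centre by centre as well as pooled.

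The article names no effect-size index for the power calculation. It gives no significance level for it, no event rate, no intraclass correlation and no attrition rate.

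**The concern.** Cohen's small and medium labels are standardised distances. For a continuous scale they fix the power once the sample size is known. For a proportion they do not: the absolute and relative change that they stand for depends on the control risk, and for a rare event a large standardised reduction may not be attainable at all. The article nevertheless extends one statement to every outcome, and those outcomes include ones that can be analysed as rare events at 250 pupils per arm.

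Reducing suicidal behaviour is one of the stated objectives (Objectives, item iii), and results are planned for each centre. A reader who trusts the statement could read a null result on suicide attempts in one country as evidence against a medium effect. At plausible event rates the design gives no such assurance.

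**Working it through.** **Inputs.** From the article: 250 per arm in a centre and 2,750 per arm pooled, with each active arm compared with an equal-sized control arm. Assumed, because the article does not give them:
- A two-sided 5% test, in line with the 95% interval.
- Cohen's values of 0.2 (small) and 0.5 (medium) for d or h.
- No clustering and no attrition, which favours the plan.
- A 12-month control risk of 1–4%.

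The only related figure in the article is the Background's 100 to 200 attempts per suicide at ages 15–24. With an assumed suicide rate of 5–15 per 100,000 per year, that gives 5 × 100 = 500 to 15 × 200 = 3,000 attempts per 100,000, or 0.5–3% a year.

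**Step 1: the plan's own figure.** Power = Φ(d·√(n/2) − 1.96).
- Centre: 0.5 × √125 = 5.59, so power is 99.99%.
- Pooled: 0.2 × √1,375 = 7.42, so power is above 99.99%.

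The numbers needed for 80% power are 63 and 393 per arm. In standardised units the claim is therefore reproduced. It survives an assumed design effect of 1.39–2.95 (schools of 40, intraclass correlation 0.01–0.05), with 90% or more at both levels. It would not survive every clustering assumption: schools of 125 with a correlation of 0.05 give 55% and 79%.

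**Step 2: does the effect exist on Cohen's h?** h = 2·arcsin√p₁ − 2·arcsin√p₂. The largest possible reduction has p₂ = 0.
- Medium: h = 0.5 needs p₁ ≥ sin²(0.25) = 6.1%.
- Small: h = 0.2 needs p₁ ≥ sin²(0.1) = 1.0%.

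On Cohen's w with equal arms, w = √(p₁/(2 − p₁)) when p₂ = 0, and the limits are 16.5% (w = 0.3) and 2.0% (w = 0.1).

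Where a small effect exists, p₂ = sin²(arcsin√p₁ − 0.1):

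| Control risk | Risk after a small effect | Relative reduction |
|---|---|---|
| 1% | 0% | 100% |
| 2% | 0.175% | 91% |
| 3% | 0.55% | 82% |
| 4% | 1.02% | 74% |
| 5% | 1.57% | 69% |
| 10% | 4.84% | 52% |

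**Step 3: the same labels as odds ratios.** ln(OR) = −d·π/√3 gives OR 0.404 for medium and 0.696 for small. Power = Φ(|p₁ − p₂| / √[(p₁(1−p₁) + p₂(1−p₂))/n] − 1.96).

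Worked example at 2%, one centre: p₂ = 0.817%, difference 1.183 points, standard error 1.053 points, ratio 1.12, power 20%. Pooled: p₂ = 1.40%, difference 0.600 points, standard error 0.349 points, ratio 1.72, power 41%.

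| Control risk | Expected control events, one centre | Power, OR 0.40, 250 per arm | Power, OR 0.70, 2,750 per arm |
|---|---|---|---|
| 1% | 2.5 | 12% | 23% |
| 2% | 5 | 20% | 41% |
| 3% | 7.5 | 28% | 56% |
| 4% | 10 | 35% | 68% |
| 5% | 12.5 | 42% | 77% |
| 10% | 25 | 70% | 96% |

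Power passes 80% at a control risk of about 5.5% pooled and about 13% in a single centre. The normal approximation is rough at 2.5 to 10 events, but the shortfall from 80% is far larger than that roughness.

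**Step 4: the most a single centre could show.** If every event were prevented in the intervention arm, power at 250 per arm would be about 35% at 1%, 62% at 2% and 79% at 3% control risk.

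**The case against.** The strongest reply is that the article never fixes suicide attempt as a binary endpoint. The Paykel scale covers ideation as well as behaviour (Baseline assessment of pupils), and the logistic regression is for an unnamed event. Analysed as a score, the outcome falls under Step 1 and the claim stands. For a commoner ideation endpoint, the odds-ratio figures improve and pass 80% at the risks given in Step 3. This stands, and it is why the point is limited to low-frequency binary outcomes. It does not rescue a sentence that covers every outcome.

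Second, the pooled half of the sentence is not false on h. Wherever h = 0.2 exists, 2,750 per arm gives nearly complete power. This also stands. That half is uninformative for a rare event, and it fails only if the label is read as an odds ratio. The conversion from d to an odds ratio is mine; the article says only that odds ratios will be reported.

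Third, a condensed article may leave power by endpoint to a fuller document. That is fair for a missing base rate or design effect. Here, though, the article makes a positive statement about all outcomes, and it is that statement which does not hold.

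A reader might also infer that the pooled trial would probably miss a halving of attempts. The article does not support that. A fall from 2% to 1% is h = 0.083, below Cohen's small, so the plan never claimed to detect it, and its power at 2,750 per arm is 86%. It drops to 67% only under an assumed 20% attrition and design effect of 1.3 (2,750 × 0.8 / 1.3 ≈ 1,692 per arm).

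**Conclusion.** The power statement holds in standardised units for continuous scales, before clustering. It does not hold for low-frequency binary outcomes.

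Within a centre it fails on h, on w and on the odds-ratio reading whenever the control risk is about 6% or less. At an assumed 1–4%, a medium reduction on h is impossible and OR 0.40 has 12–35% power. At the pooled level the statement says little on h, and power is 23–68% on the odds-ratio reading at the same risks.

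These figures rest on an assumed control risk, since the article states none, and on ideal conditions. Because schools are randomised and some pupils will be lost, real power would be lower.

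Two stronger readings should be avoided. One is that the claim cannot hold for suicidal behaviour at all: that depends on the event rate and on how the Paykel outcome is scored. The other is that a small effect always means near-elimination: that fits a control risk of about 1–2%, and at 10% a small effect is a 52% reduction. The impossibility also concerns reductions only, not increases.

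**What to change.** In the Data analysis section:
- Remove the words that extend the power statement to every outcome, and confine the small and medium wording to continuous scales, naming the index used.
- For binary suicidal events, state the detectable odds ratio or risk difference at centre and at pooled level over a stated range of control risk (for example 1–4%), allowing for school clustering and attrition with the assumed values shown.
- Acknowledge that single centres are not powered for rare events.

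The cost is one rewritten paragraph. Enrolment and design are unchanged; the stated power becomes less favourable.

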### Inclusion and exclusion criteria

Schools and adolescents in the study areas are eligible to participate if they meet all the following criteria:

(1) the school authority agrees to participate;

(2) the adolescents attend non-specialist public schools;

(3) school contains at least 40 pupils aged 15;

(4) school has more than two (3+) teachers for pupils aged 15;

(5) no more than 60% of pupils are of either sex;

(6) informed consent from parents and pupils is obtained.

If the school-based adolescents meet the following exclusion criteria, they are ineligible to participate:

(1) the school authority refuses to participate;

(2) the adolescents attend a specialist and/or independent or private school;

(3) the adolescents attend single-sex schools;

(4) a school has fewer than 40 pupils aged 15;

(5) the parents of pupils in a participating school, or the pupils themselves, have refused to sign the consent document.

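### The printed power of more than 80% within individual centres counts pupils and shows no allowance for randomising schools, so the design as described does not secure it

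*Protocol article*

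**What the plan says.** All references are to the protocol article.

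- **Unit of randomisation** (Population and sampling procedures): "Schools are randomized on the basis of their size category and sequentially assigned to respective intervention and control arms". Each school delivers one intervention only, so arm is nested in school.
- **Sample size** (same section): "The target sample for each intervention 'arm' as well as for the control 'arm' is 250 pupils". That is 1,000 pupils per country and 11,000 overall. No number of schools is given.
- **School eligibility** (Inclusion and exclusion criteria): "school contains at least 40 pupils aged 15". In a selected school, every class with a majority of 15-year-olds is surveyed.
- **Power** (Data analysis): "Power calculations adhere to the widely accepted proposals made by Cohen (1988) [57] for detection of small, medium and large effects". On that basis the article claims, whatever the outcome measure, "more than 80% statistical power to detect medium effects within the individual centers and small effects at the aggregate level of centers".
- **Surplus** (Data analysis): "The SEYLE study sample potentially exceeds the sample size requirements in order to detect statistically significant changes". The surplus is said to cover centres that recruit short, attrition and missing data. Clustering is not mentioned.
- **Use**: analyses are planned both by centre and pooled, and variation in effect across the 11 centres is to be examined.

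**The concern.** Pupils in one school tend to resemble each other, and each school contributes to one arm only. The information in a comparison of arms therefore depends on the number of schools and the ICC as well as on the number of pupils. A power statement built on pupil counts overstates what a valid test can detect, and most of all inside a single centre, where the schools in each arm are likely to be few.

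At stake is how single-country results will be read. A reader told that each country has more than 80% power for a medium effect on every outcome may take a null result in one country as evidence of no effect. The sentence on surplus sample size adds to this by suggesting there is room to spare after attrition.

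**Working it through.** **Inputs from the article.** 250 pupils per arm per centre; 2,750 per arm on aggregate ("The control arm contributes 2,750 adolescents (250 per site) to the total sample"); schools randomised; at least 40 pupils aged 15 per school.

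**Assumptions.** Medium d = 0.5 and small d = 0.2 with SD 1 (the article names the categories but prints no values). Two-sided alpha 0.05, in line with the planned 95% confidence intervals. ICC from 0.01 to 0.10. k schools of equal size per arm per centre. No attrition unless stated.

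**Step 1: reproduce the printed claim.** With independent pupils the noncentrality is d × √(n/2).
- Within a centre: 0.5 × √125 = 5.59, and power = Φ(5.59 − 1.96) = 99.99%. Only 63 per arm are needed for 80%.
- Aggregate: 0.2 × √1375 = 7.42, and power exceeds 99.99%. Only 393 per arm are needed.

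The claim reproduces with much room to spare, as a calculation on independent pupils.

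**Step 2: how many schools?** 250/40 = 6.25, so about 6 or fewer schools per arm per centre if most eligible pupils take part, and more if consent is low. This is an inference; the article gives no count.

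**Step 3: add clustering.** With m = 250/k pupils per school:
- design effect DE = 1 + (m − 1) × ICC
- effective size n_eff = 250/DE
- noncentrality = 0.5 × √(n_eff/2)
- power from the noncentral t with 2(k − 1) df

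Example, k = 4 and ICC 0.05: m = 62.5; DE = 1 + 61.5 × 0.05 = 4.075; n_eff = 250/4.075 = 61.3; noncentrality = 0.5 × √30.7 = 2.77; critical t on 6 df = 2.447; power = 64%.

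| Schools per arm | ICC 0.01 | 0.02 | 0.03 | 0.05 | 0.10 | Largest ICC keeping 80% |
|---|---|---|---|---|---|---|
| 2 | 52% | 39% | 31% | 23% | 15% | none |
| 3 | 87% | 73% | 62% | 47% | 29% | 0.015 |
| 4 | 95% | 87% | 79% | 64% | 42% | 0.029 |
| 5 | 98% | 93% | 88% | 75% | 53% | 0.042 |
| 6 | 99% | 96% | 92% | 82% | 61% | 0.055 |

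With 2 schools per arm, 2 df alone cap power at 79% even when the ICC is zero (noncentrality 5.59 against a critical value of 4.303).

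**Step 4: sensitivity.**
- A pooled four-arm model with 4(k − 1) df gives 79.5% for 2 schools at ICC 0.01, 86% for 4 at 0.03, 72% for 4 at 0.05 and 81% for 5 at 0.05.
- With 30% attrition (an assumed figure), 4 schools at ICC 0.03 give 73% and 6 at 0.05 give 78%.
- More schools, as low consent would imply: 8 schools give 91% at ICC 0.05; 12 give 87% at ICC 0.10.

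**Step 5: aggregate claim.** d = 0.2, 11k schools per arm, noncentral t with 22k − 12 df. At ICC 0.05, power is 76% with 2 schools per arm per centre (75% with 22(k − 1) df), 90% with 3, 95% with 4 and 99% with 6. At ICC 0.10 it is 50% with 2, 78% with 4 and 91% with 6.

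**The case against.** The strongest reply is that the outcome turns on two figures the article does not print. A condensed article may leave the ICC and the number of schools to the full protocol or the analysis plan, so their absence alone is no fault. This stands. The point rests instead on what is printed: a power figure for every outcome in every centre, and a list of allowances that leaves out clustering.

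A reader might infer that the within-centre power is simply not achieved. The documents do not support that. The large slack in 250 pupils per arm absorbs a low ICC: 3 schools at 0.01 give 87%, 4 at 0.02 give 87% and 6 at 0.05 give 82%.

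Nor is 6 schools a ceiling. The 40-pupil minimum counts pupils of that age in the school, not participants, and both parents and pupils must consent. Smaller participating clusters would mean more schools and more power.

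The two-arm df are also the less favourable choice. Pooled four-arm df help, and adjustment for baseline could lower the residual ICC. Both are fair, but with 4 schools at ICC 0.05 the pooled df still reach only 72%.

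A reader might also infer that a country with 2 schools per arm cannot be tested at all. It can, on 2 df; the test is weak.

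Finally, pupil-level tests do not rescue the claim. They would keep nominal power only by inflating type I error: with 4 schools at ICC 0.03, DE = 2.845 and the true error is 2 × [1 − Φ(1.96/√2.845)], about 25%.

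**Conclusion.** The concern holds in a conditional form. The within-centre statement matches a calculation on independent pupils and is not secured by a design that randomises schools. With about 6 or fewer schools per arm, it stays above 80% only up to an ICC of about 0.015 with 3 schools, 0.03 with 4, 0.04 with 5 and 0.055 with 6. With 2 schools per arm, a two-arm school-level test cannot reach 80% at any ICC. Because the claim covers all outcome measures, the ICC would have to be low for each of them, or the schools numerous.

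The aggregate claim for small effects is less exposed. It falls below 80% only towards few schools or a high ICC, such as 2 schools at 0.05 or 4 at 0.10.

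These sizes rest on d = 0.5 and 0.2, equal cluster sizes, an assumed ICC range and an inferred number of schools.

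**What to change.** - Recompute power with a design effect, using the planned number of schools per arm in each country and a stated ICC range.
- Replace the within-centre statement of more than 80% for all outcome measures with the range obtained, or limit it to the outcomes and centres where it holds.
- Qualify the sentence that the sample may exceed requirements, so that clustering is among the things the surplus has to cover.

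This needs no extra pupils and no change to how schools or classes are selected. The only cost is a less favourable stated figure.

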### Baseline assessment of pupils

The baseline evaluation questionnaire, completed within the confines of the classroom, is followed up with a post-intervention evaluation questionnaire 3- and 12-months post-baseline to study changes in attitudes, lifestyles, behaviors and mental health problems of pupils. The baseline assessment obtains data on lifestyles, behaviors, values, mental health and suicidality. Data are collected by means of structured questionnaires, including:

(i) the *Global School-Based Pupil Health Survey *(GSHS) [42], which assesses lifestyles and risk-taking behaviors;

(ii) the *WHO Well-being Scale *(WHO-5) [43], which evaluates mood (good spirits, relaxation), vitality (being active and waking up fresh and rested) and general interests (being interested in things);

(iii) the *Beck Depression Inventory *(BDI) [44], which measures depressive symptoms;

(iv) the *Paykel Suicide Scale *(PSS) [45], which determines suicidal ideation and suicidal behavior;

(v) the *Strengths and Difficulties Questionnaire *(SDQ) [46], which collects information on emotional symptoms, conduct problems, hyperactivity and/or inattention, peer relationship problems and pro-social behavior;

(vi) the *Deliberate Self-Harm Inventory *(DSHI) [47], which evaluates deliberate self-harm behavior;

(vii) the *Young's Diagnostic Questionnaire *(YDQ) [48] for Internet Addiction, which identifies Internet dependency among adolescents;

(viii) questions from the *European Values Study *(EVS) [49], which examines values, such as religion, family, marriage, work and friendship;

(ix) specific items developed or modified for the SEYLE study, concerning reading, music, and internet habits, as well as coping, trauma and bullying, stressful life events, stigma and discrimination, peer and parent-child relations, children's physical health, alcohol and substance use, and future outlook.

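### When diagnostics fail, continuous scales switch to rank tests that cannot adjust for baseline score, school-size category or school; adjustment is stated only for odds ratios

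*Protocol article*

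**What the plan says.** The Data analysis section of the protocol article starts by checking whether continuous variables suit parametric tests; it does not name those tests. It then gives a rule: "In cases where the diagnostics indicate that the reliability of the parametric tests may be significantly undermined", a non-parametric test takes over. The candidates follow: "These include the Mann-Whitney test, the Kruskal-Wallis test, the Wilcoxon test and Friedman's ANOVA".

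Covariate adjustment appears in one place only, the logistic regression of events on arm, where an adjusted odds ratio with unnamed covariates is promised. The interval estimate is tied to the same analysis: "The odds ratio, with its 95% confidence interval, is used as the measure of relative risk".

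Other sections show what is available. Baseline and follow-up use largely the same questionnaires, "to study changes in attitudes, lifestyles, behaviors and mental health problems of pupils" (Baseline assessment of pupils; 3- and 12-month follow-up assessment). A pupil code links each pupil's records (Research Ethics). Schools are the randomised units, and they are randomised by size category (Population and sampling procedures). The objectives and Study design define evaluation as comparison with a control group.

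**The concern.** The rule makes the method depend on how the observed data look, and the method it switches to can do less. In their ordinary form the four rank tests take no covariate and have no school term. Mann-Whitney and Kruskal-Wallis compare arms but ignore baseline unless they are run on change scores, which the text does not say. Friedman's test compares occasions within the same pupils. The Wilcoxon test most naturally means the signed-rank test here, since Mann-Whitney already covers the two-sample case; it then also compares occasions. Neither contains an arm-versus-control contrast, so neither can answer the trial's question.

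Two things are at stake. Baseline score usually explains part of the follow-up score, so leaving it out costs precision. And because whole schools are randomised, few of them per arm in each country, arms will differ at baseline by more than under randomisation of pupils. An unadjusted comparison carries part of that difference into the result. Symptom scales in a general school population may well be skewed (an assumption), so the fallback may be used often.

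**Working it through.** **Inputs from the protocol article.**
- Pupils per arm per country: "The target sample for each intervention 'arm' as well as for the control 'arm' is 250 pupils".
- Aggregate arm size: "The control arm contributes 2,750 adolescents (250 per site) to the total sample". Each active arm is 8,250 / 3 = 2,750 as well.
- Power claim: "more than 80% statistical power to detect medium effects within the individual centers and small effects at the aggregate level of centers".

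**Assumptions, because the article prints no figure.** Cohen's d = 0.5 (medium) and 0.2 (small); two-sided alpha 0.05; k = 2 to 6 schools per arm per country; intraclass correlation (ICC) 0.02 to 0.05; pupil-level baseline-to-follow-up correlation r = 0.5 to 0.7.

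**1. The plan's own figure.** Power ≈ Φ(d·√(n/2) − 1.96), with no clustering and no baseline adjustment.
- Centre, d = 0.5, n = 250: 99.99% (80% needs 63 per arm).
- Aggregate, d = 0.2, n = 2,750: above 99.99% (80% needs 393 per arm).

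The stated 80% is reproduced as a lower bound when clustering is ignored.

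**2. Chance baseline difference between two arms.** With m = 250/k pupils per school and design effect DE = 1 + (m − 1)·ICC, the SD of the difference in baseline means, in outcome SDs, is √(2·DE/250) within a centre. Over 11 centres it is divided by √11 = 3.317. The part carried into an unadjusted follow-up comparison is about r times this.

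| k | ICC | DE | SD, centre | SD, 11 centres |
|---|---|---|---|---|
| 6 | 0.02 | 1.81 | 0.120 | 0.036 |
| 4 | 0.05 | 4.08 | 0.181 | 0.054 |
| 2 | 0.05 | 7.20 | 0.240 | 0.072 |

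Carried part:
- Centre: 0.5 × 0.120 = 0.06 to 0.7 × 0.240 = 0.17, or 12% to 34% of a medium effect of 0.5.
- Aggregate: 0.5 × 0.036 = 0.018 to 0.7 × 0.072 = 0.051, or 9% to 25% of a small effect of 0.2.

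**3. Precision.** Adjusting for baseline multiplies residual variance by 1 − r²: 0.75 at r = 0.5 and 0.51 at r = 0.7, a reduction of 25% or 49%. This is the factor for individually randomised pupils. If the same reduction held at school level, with 60 pupils per school and ICC 0.05 (DE = 3.95), power for d = 0.5 in one centre would rise from 80% to 90% at r = 0.5.

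**4. Does the power claim depend on adjustment?** Replace n by n/DE.
- With 40 to 60 pupils per school and ICC 0.01 to 0.05, unadjusted power is 80% to 99.7% in a centre and 96% or more overall.
- With 2 schools per arm and ICC 0.05 (DE = 7.2), it is Φ(0.5·√(250/14.4) − 1.96) = Φ(0.12) ≈ 55% in a centre and Φ(0.2·√(2,750/14.4) − 1.96) = Φ(0.80) ≈ 79% overall.

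That shortfall comes from clustering, not from the missing baseline term.

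**The case against.** The strongest reply is that the rank tests are a conditional fallback in an open-ended list. The parametric route is unnamed and could be analysis of covariance or a mixed model, and a journal article may leave that to a full protocol or analysis plan that is not shown. This stands. A reader might infer that continuous outcomes will in general be compared without baseline; no sentence says so. Nor does the text show that the baseline score is discarded. The stated aim is to study change, a rank test on change scores would use baseline, and paired tests use it directly.

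A reader might also infer that a significant change within one arm will count as an intervention effect. No section says that, and the objectives point the other way. Paired tests are legitimate for describing change.

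On size, it is tempting to set the within-centre imbalance beside a small effect. The article seeks small effects only at aggregate level, where the imbalance is several-fold smaller. It is also tempting to turn 1 − r² into 33% to 96% more pupils (1/0.75 = 1.33; 1/0.51 = 1.96). That ignores clustering: the gain depends on school-level correlation too, and extra pupils in the same schools do not buy equal precision.

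Country is not simply ignored, since analyses are also run by centre. Finally, chance imbalance under randomisation is covered by correct standard errors.

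What remains is not just missing detail. The article does state a rule, and that rule leads away from any baseline-adjusted contrast with control.

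**Conclusion.** The point holds as a recommendation on the choice of method. For any continuous scale that fails the diagnostics, the written rule leads to a test that, as named, cannot adjust for baseline score, school-size category or school, and in one or two of the four cases makes no comparison with control. An adjusted estimate with an interval is stated only for odds ratios.

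The cost is precision and random error, not systematic bias. The carried imbalance has an SD of about 0.06 to 0.17 outcome SDs in a centre and 0.02 to 0.05 overall: noticeable beside a medium effect in one centre, modest beside a small effect overall. It does not by itself undo the power claim. All these sizes rest on assumed ICC, schools per arm, r and Cohen values. The text does not support a finding that the trial will ignore baseline or infer efficacy from within-arm change.

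**What to change.** For each continuous scale, estimate the arm-versus-control difference at follow-up, with its 95% confidence interval, from one linear mixed model. Use the pupil's baseline score, country and school-size category as covariates and school as random effect. For skewed scales keep this model and use cluster-robust or school-level bootstrap standard errors, in place of the data-driven switch to rank tests. Keep the Wilcoxon and Friedman tests for describing change over time only. In the logistic models, enter the baseline value of the outcome and the randomisation factors as named covariates.

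Every variable is already collected and linked by pupil code, so the cost is analysis wording and programming. With few schools per arm in a centre, cluster-robust errors need a small-sample correction, and centre-level results should be read with that limit in mind.
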